### Primary outcome

The primary outcome of this study is the completion of cervical cancer screening test within 6 months of the baseline assessment. Participants will be interviewed using the survey questionnaire and tracked via health records review for completing the screening service. The screening proportions will be determined for each study arm at the baseline & end line. The difference in the screening proportions between intervention and control arms will be calculated. Finally, the effectiveness of the intervention will be measured as a difference of the differences in the screening uptake between the study arms.

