### Secondary outcomes

We will also assess the progress of participants’ knowledge and attitude by measuring their knowledge and attitude at baseline and end line. The effect of the intervention on participants’ knowledge and attitude will be determined and compared between the study arms.

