### Sampling procedure

Sixteen clusters (kebeles) will be selected from the two study districts where cervical cancer screening service is currently available. Sixteen clusters are taken based on the recommendation that taking fewer subjects from many clusters give better representation of the sample than taking many participants from fewer clusters. The clusters will be randomly assigned in to intervention and control groups. Census will be carried out in the selected Kebeles to identify women who are eligible for screening and create sampling frame. Then, simple random sampling technique will be performed to select study participants from each arm. We will select equal number of participants from each cluster which consequently leads to selection of 18 participants per cluster. The same sample of participants will be used at the end of the intervention phase, six months later, to measure the outcome variables (Fig 2).

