### Statistical analysis

Base line screening proportions will be computed after randomization and before the intervention administration to measure the last 5 years screening performances of women in both arms with 95% confidence interval. The groups will be examined and compared at base line for any statistical differences in terms of base line participants’ characteristics and their screening experiences. The baseline characteristics will be compared using chi-square test for categorical variables and the results will be indicated in chi-square value with p-value. The continuous variables of the groups at the baseline will be compared using independent sample t-tests and the results will be shown as mean, standard deviation and p-value. A one-sided P value of 0.05 will be used to determine statistical significance.

After completing the end line survey, proportions of women that will be screened during the trial period will be calculated with the corresponding confidence interval. We will also compare the before and after intervention scores of participants’ knowledge and attitude of intervention group using paired sample t-test. A similar analysis will be done for the control group to compare the before and after intervention knowledge and attitude scores. Then we will employ the independent-sample t-test to determine the effectiveness of the intervention on knowledge and attitude by comparing participants’ knowledge and attitude scores between the two groups. The results will be computed in terms of the value of the test statistic, means, standard deviations and p-value at 5%.

Finally, we will use Generalized Estimating Equation analysis technique to test the independent effect of the intervention on the uptake of cervical pre-cancer screening services. The effect size of the intervention, confidence interval and associated P-value will be determined during the analysis. Intention to treat approach will be employed to analyze the data.

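### Knowledge and attitude are framed as progress from baseline, but the between-arm test of effectiveness names no change score or baseline adjustment, which gives up precision and lets part of any chance baseline gap into the estimate

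*Protocol article*

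**What the plan says.** Secondary outcomes sets the aim: "We will also assess the progress of participants’ knowledge and attitude by measuring their knowledge and attitude at baseline and end line". It adds that the effect on both will be compared between arms. Sampling procedure makes this a cohort: "The same sample of participants will be used at the end of the intervention phase, six months later, to measure the outcome variables". Each woman followed up therefore has her own baseline score.

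Statistical analysis then sets out three steps that could involve these scores.

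- Baseline characteristics are compared between arms, with t-tests for continuous variables. Nothing is said about what follows from a difference.
- Within the intervention arm, the plan is to "compare the before and after intervention scores of participants’ knowledge and attitude of intervention group using paired sample t-test". The same is done separately for controls.
- Between arms, "we will employ the independent-sample t-test to determine the effectiveness of the intervention on knowledge and attitude", and this is done "by comparing participants’ knowledge and attitude scores between the two groups".

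The generalized estimating equation in the same section is assigned to screening uptake only. For the primary outcome, by contrast, the baseline is part of the effect measure: "the effectiveness of the intervention will be measured as a difference of the differences in the screening uptake between the study arms".

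**The concern.** The outcome is described as progress, and the data needed to measure progress in each woman will be in hand. The one test given the task of deciding effectiveness is nevertheless described without them. The paired tests use the baseline, but each looks at a single arm and cannot compare the arms.

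Only 16 kebeles are randomised. The blocks are formed alphabetically within district, which does nothing to balance prior knowledge or attitude between kebeles. A chance difference at baseline is therefore likely to be visible, and because scores on the same woman are usually correlated over time, part of it reappears at end line. At stake are the precision of the two secondary results and how they can be read when the arms happen to start apart.

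**Working it through.** **The plan's own figure.** The inputs are in Sample size: 15.5% against 35.5%, one-sided 5%, 80% power, design effect 2, 5% non-response. The pooled two-proportion formula gives 58 per arm, or 68 with continuity correction. Then 68 × 2 = 136, and 136 / 0.95 = 143.2, rounded up to 144 per arm. That makes 288 in total, which agrees with the protocol and with 16 kebeles × 18 women. No sample size is stated for knowledge or attitude.

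**Size of a chance baseline gap.** Scores are in SD units.

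- Assumption: the design effect of 2, stated for screening uptake, also holds for the scores. With 18 women per kebele this implies an intracluster correlation of (2 − 1)/(18 − 1) = 0.059.
- SE of the gap = √(2 × (1/144 + 1/144)) = √(4/144) = 0.167 SD.
- 95% range: ±1.96 × 0.167 = ±0.33 SD.
- Probability of a gap beyond 0.2 SD in either direction: 0.2/0.167 = 1.2, so 23%.

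**How much passes into the estimate.** If the test is on end-line scores, a fraction of about r of the gap carries over, where r is the baseline to end-line correlation. The documents give no value for r, so a range is assumed.

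- r = 0.3: 0.3 × 0.167 = 0.05 SD for a one-SE gap.
- r = 0.7: 0.7 × 0.167 = 0.12 SD for a one-SE gap.

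**Simulation check.** This used 8,000 trials with no intervention effect, each with 16 kebeles × 18 women and intracluster correlation 0.059. The adjusted analysis is a regression of kebele end-line means on arm and kebele baseline means.

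| Correlation: kebele / woman | Share of gap carried over, unadjusted | SD of estimate, unadjusted | SD of estimate, adjusted | Gain |
|---|---|---|---|---|
| 0.3 / 0.3 | 0.29 | 0.165 | 0.165 | about nil |
| 0.5 / 0.5 | 0.50 | 0.165 | 0.149 | 10% |
| 0.7 / 0.5 | 0.61 | 0.166 | 0.136 | 18% |
| 0.8 / 0.7 | 0.75 | 0.167 | 0.114 | about 30% |

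After adjustment, the correlation between the estimate and the baseline gap is about zero in every row (−0.004 to 0.010). The large-sample factor √(1 − r²) gives 0.954 at r = 0.3 and 0.714 at r = 0.7, that is, gains of 5% and 29%. At r = 0.3 the small gain disappears in the cluster-level analysis, where the baseline slope has to be estimated from 16 means.

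**Change scores as an alternative.** At r = 0.3 a change-score comparison has SD 0.198 against 0.165 for end-line scores, and it over-corrects: 0.71 of the gap returns with the opposite sign. Change scores fit the word progress but are less reliable than adjustment when r is low.

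**Whether adjustment alone is enough.** With a design effect of 2, an ordinary t-test has a true two-sided 5% error rate of 16.6% (12.2% for a one-sided 5% test). Adding the baseline in an ordinary regression on individual women leaves the two-sided rate at 13% to 17% in the simulation. The cluster-level adjusted analysis gives 4.5% to 5.2%. The baseline term therefore has to sit in an analysis that respects clustering.

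**The case against.** Four points can be made for the plan.

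1. The sentence on the t-test says neither raw nor end line. It follows directly on the before-and-after comparisons, and the primary outcome is a difference in differences, so change scores may have been meant. This stands as a limit. End-line scores are the plain reading, but a reader who concludes that the plan expressly commits to raw end-line scores goes beyond the text. Under either reading the text has to say which score is compared.

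2. A reader might infer that chance baseline differences are mistaken for an effect and that the test is biased for that reason. The documents do not support this. Under randomisation, end-line and change-score comparisons have the same expected treatment difference, and a correct standard error already covers chance imbalance. What remains is imbalance conditional on the gap that actually occurs, and lost precision.

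3. A reader might also infer that effectiveness will be claimed from a significant change in one arm and none in the other. The plan gives that role to the between-arm test, so the paired tests are at most open to misreading. Nor is the baseline wholly confined to them: the baseline comparison of the arms could reveal a gap, though it leads to no adjustment.

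4. Covariate adjustment of secondary outcomes is often left to an analysis plan, and none is shown. But this protocol itself names the test and the quantity compared, and the named test takes no covariate. An analysis plan would have to replace it, not merely add detail.

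**Conclusion.** The point holds as a mismatch and an avoidable loss. The outcome is framed as progress in the same women, while the deciding between-arm test names neither change nor baseline adjustment. The comparison is unbiased on average, and omitting the baseline does not by itself make it invalid. The cost is a carry-over of about 0.05 to 0.12 SD for a one-SE baseline gap, and a forgone precision gain of nil to about 30%.

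These sizes rest on two assumptions: that the design effect of 2 applies to the scores, and that the correlations lie in the ranges shown. If the true correlation is near 0.3, there is almost no precision to gain at cluster level, and the benefit is limited to removing the carry-over. The failure of the same t-test to allow for clustering is a separate fault with larger consequences for the error rate, but both can be corrected in one step. Because these are secondary outcomes, the correction is advisable and does not bear on the primary analysis.

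**What to change.** Replace the independent-sample t-test for knowledge and attitude with a between-arm comparison of the end-line score, adjusted for the woman's own baseline score. Fit it in a model that allows for kebele clustering: a mixed model or generalized estimating equation with a small-sample correction, or a cluster-level analysis. Include district, since allocation was stratified by it. State that this adjusted difference is the test of effectiveness for each score, and that the within-arm paired results are descriptive only.

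The cost is a rewritten paragraph and a different model in the software already named. Baseline scores are already to be collected, so no new data are needed and the sample size of 288 is unchanged.

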### Randomization

The clusters or kebeles are the units of randomization in our study. Initially, eight non-adjacent clusters from each district will be identified from the two districts. Before randomization, we will stratify the clusters by the study districts and create separate list of clusters alphabetically for each district. The stratification will be done to evenly distribute any known and unknown district level confounders across the study arms. Each cluster will be assigned a unique cluster code. Then, the statistician will assign the eight clusters in to two blocks of size 4 according to the order they appeared alphabetically. The statistician will randomly select the randomization sequence of clusters for each block using the sealed lots of the six possible permutations within the block.

The clusters in each block will be randomly assigned to intervention and control arms according to the randomization sequence evident by the selected permutation within in the block for the stratum. We will repeat the same process for blocks of clusters in the other stratum. Consequently, four clusters will be obtained from each district which will form eight clusters to the intervention arm and eight clusters to the control arm maintaining 1:1 random allocation ratio. Both the stratification and randomization techniques will help actual and potential confounding factors distribute evenly across the study arms which will eventually ensure comparability of the arms.

The statistician will be made unaware of the actual study arms to mask the knowledge about which group will receive the intervention and which group will receive the usual care. This will be achieved by representing the study arms and clusters by confidential codes. Health extension workers will carry out identification of eligible participants’ for the study and subsequent intervention administration activities. Assessors will also be made blind to the nature of clusters with respect to intervention administration.

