### Sample size

As a requirement, we identified the proportion of current cervical cancer screening service utilization from existing literatures to be 15.5% among age eligible women [18]. This has been taken as a baseline proportion for the study and considered to be the proportion for the control arm. We will expect an absolute difference of 20% increase in screening proportions between the study arms which gives the effect size or change in screening proportion due to the intervention to be 0.2. This produces the expected end line proportions of cervical cancer screening for the study to be 35.5% and considered as the proportion for the intervention arm.

The power of the study to detect the real statistical difference is set to be 80% and 5% significance level for one-tailed test has been used. We also considered the design effect of 2 to adjust for the loss of variability that would happen due to the effect of clustering and 5% as a compensation for incomplete and non-response rates that might happen during the data collection time. Considering the above assumptions and parameters, we arrived at a total of 288 study participants basically with the help of Gpower software. The required number of clusters we determined for the study is sixteen.

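### The primary GEE rests on 16 kebeles with no stated small-sample correction; in its standard robust form the one-sided 5% test would run at about 7.3%

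*Protocol article*

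**What the plan says.** The Statistical analysis section of the Protocol article names the primary method in one sentence: "we will use Generalized Estimating Equation analysis technique to test the independent effect of the intervention on the uptake". It adds that an effect size, a confidence interval and a P-value will be reported by intention to treat. It does not state the working correlation, the type of standard error, the reference distribution or the covariates.

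The design around it is fixed:

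- The Randomization section ends with "eight clusters to the intervention arm and eight clusters to the control arm maintaining 1:1 random allocation ratio", and says "Before randomization, we will stratify the clusters by the study districts".
- Sampling procedure gives "selection of 18 participants per cluster", so 16 × 18 = 288 women.
- Sample size says "5% significance level for one-tailed test has been used". Statistical analysis repeats this, in its paragraph on baseline comparisons: "A one-sided P value of 0.05 will be used to determine statistical significance".
- Data management names SPSS or Stata as the software.

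**The concern.** GEE inference normally uses a robust (sandwich) variance, whose justification is asymptotic in the number of clusters, not of women. With 16 clusters there are two problems. The sandwich divides residual variation by the number of clusters per arm (8) rather than by its degrees of freedom (7), so the variance is biased downward. In addition, a variance estimated from so few clusters calls for a t rather than a normal reference. Both push the rejection rate above its nominal level and make the confidence interval too short.

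The Abstract says the findings are to inform regional or national scale-up, so the real error rate of the primary test matters. The kebeles are also stratified by district, and the analysis text does not mention district. That is a separate question of precision and calibration.

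**Working it through.** **Inputs from the article.** 8 + 8 kebeles; 18 women each; control uptake 15.5%; intervention uptake 35.5%; design effect 2; one-sided 5%; power 80%; 5% non-response; two districts with 8 kebeles each.

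**Assumptions not in the article.** Beta-binomial uptake within kebeles; kebele as the GEE cluster; robust standard error with z reference for the uncorrected case; illustrative district gaps.

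**Step 1: the plan's own sample size.** The one-sided two-proportion formula with pooled proportion 0.255 gives

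n = [1.645·√(2·0.255·0.745) + 0.842·√(0.155·0.845 + 0.355·0.645)]² / 0.20² ≈ 57.7 per arm.

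The continuity correction, (n/4)·[1 + √(1 + 4/(n·0.20))]², raises this to 68. Then 68 × 2 arms × 2 = 272, and 272 × 1.05 ≈ 286, which rounds up to 16 × 18 = 288. The figure is reproduced. This normal-theory route makes no allowance for limited cluster degrees of freedom.

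**Step 2: the intracluster correlation.** Design effect = 1 + (m − 1)·ICC, so 2 = 1 + 17·ICC and ICC = 1/17 ≈ 0.059.

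**Step 3: theory for the uncorrected test.** With 8 equal clusters per arm, the sandwich variance is 7/8 = 14/16 of the unbiased one. The uncorrected statistic exceeds 1.645 when a t variable on 14 df exceeds 1.645·√(14/16) = 1.539.

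- One-sided: P(t₁₄ > 1.539) ≈ 7.3%.
- Two-sided: the same calculation with 1.960 gives 8.8%.

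**Step 4: simulation under no effect** (200,000 runs, uptake 15.5%, ICC 1/17).

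| Test | One-sided 5% | Two-sided 5% |
|---|---|---|
| Robust SE, z | 7.3–7.4% | 8.8–9.0% |
| Robust SE × M/(M−1) factor, z | 6.7% | 8.0% |
| df-corrected variance, t(14) | 5.0% | 5.0% |
| District in model, df-corrected, t(13) | 4.9% | 4.9% |

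Varying uptake from 10% to 35.5% and ICC from 0.01 to 0.10, with and without 5% random loss, moves the uncorrected rates over 7.1–8.2% one-sided and 8.3–10.2% two-sided. The t(14) correction stays within about 4.5–5.9%. A smaller check with a fitted exchangeable GEE (1,500 runs, Monte Carlo error about 0.6–0.7 points) gave 6.6% and 8.1%. A separate 40,000-run simulation gave 5.2% for a Kauermann–Carroll type variance with t(14), and 5.0% for a t-test on the 16 kebele proportions.

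**Step 5: the role of district** (one-sided rates, uncorrected z test, allocation stratified by district, identity link for the adjusted model).

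| Gap between districts | District omitted | District included |
|---|---|---|
| 0 points | 7.4% | 8.1% |
| 5 points | 6.9% | 8.1% |
| 10 points | 5.8% | 8.1% |
| 15 points | 4.3% | 8.2% |
| 20 points | 2.7% | 8.3% |

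In the fitted logit GEE, including district without a correction gave 7.2–7.4% one-sided. Omission therefore lowers the rate, because the between-district variance that stratification has balanced stays in the error term.

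**Step 6: power.** Simulated at 15.5% versus 35.5% with ICC 1/17 and no loss, one-sided power is 88.7% for the uncorrected z test and 83.6% with the t(14) correction. By approximation with 5% loss, the effective sample is 144 × 0.95 / 2 = 68.4 per arm. That gives 85.7% with z and 82.8–83.5% with t(14).

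**The case against.** The strongest objection is that the article is silent rather than wrong. It names a method suited to clustered data, and a condensed article may leave the variance estimator, degrees of freedom and covariates to a fuller document. The phrase about an independent effect is even compatible with an adjusted model. This stands in part: the inflation occurs only if uncorrected robust output with a z reference is used. It does not remove the point, because the named method in its standard form is miscalibrated on the design the article fixes, and the remedy is known and cheap.

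Two stronger readings are tempting, and the document supports neither.

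- A reader might infer that the trial's test does run at 7–9%. The article makes no such commitment. Moreover, the upper end belongs to a two-sided test, while the protocol's test is one-sided, where the figure is about 7.3%.
- A reader might infer that the missing district term is part of the cause. Step 5 shows the opposite: with district left out, the test becomes more conservative as the districts differ, which partly offsets the inflation.

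The article also gives no confidence level for the GEE interval; its 95% refers to the baseline proportions.

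**Conclusion.** The point holds in conditional form. If the primary GEE is run on 8 + 8 kebeles with a standard robust standard error and a z reference, the one-sided 5% test runs at about 7.3%, nearly half as many false positives again as stated (7.3/5 = 1.46). A two-sided test would run at about 8.8%, so a nominal 95% interval would cover about 91%. The result rests on beta-binomial data and the ICC implied by the design effect of 2, and it changes little over the ranges tried. A model-based standard error was not examined.

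The district term is a separate matter of precision and calibration. With neither item settled, the true level depends on an unknown gap between districts: 7.4% one-sided with no gap, 2.7% with a 20-point gap.

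**What to change.** State that the primary test is a GEE with kebele as the cluster, a small-sample-corrected variance (Kauermann–Carroll or a degrees-of-freedom correction, for example) and a t reference with cluster-based degrees of freedom. A district-stratified cluster-level t-test on the 16 kebele proportions is an acceptable alternative. Separately, include district as a fixed effect. Make the two changes together, since district without the correction leaves the test liberal. Keep other covariates few, because the degrees of freedom come from 16 clusters.

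The cost is a sentence or two of analysis text and a wider interval. At the 95% level the multiplier goes from 1.960 to 2.145·√(16/14) = 2.293, about 17% wider than the uncorrected interval. One-sided power on the plan's assumptions is about 83%, above the stated 80%, and the sample size need not change. That holds for the protocol's one-sided test; the same simulation gives 72.1% if the corrected test were made two-sided.
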